### Study endpoints

The composite primary study endpoint is the incidence of MACEs after PCI for SVGD, including death from cardiac causes, non-fatal myocardial infarction, angina pectoris, target vessel revascularization (TVR) and hospitalization for heart failure.

Secondary endpoints are defined as: (1) the occurrence of the slow/no reflow, which is defined as thrombolysis in myocardial infarction (TIMI) grade 0, 1, or 2 flow within 24 h after SVG-PCI, despite successful treatment of the vessel obstruction; (2) myocardial infarction is defined as the onset of chest pain in combination with new, typical changes in the electrocardiogram and biochemical evidence of myocardial necrosis; (3)TVR is defined as a new revascularization procedure in the target vessel; (4)successful reperfusion is defined as TIMI flow grade 3 and less than 50% residual stenosis of SVG.

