**Methods/design:**

This is a prospective cohort study conducted in Tianjin Chest Hospital, China. Participants with SVGD referred for PCI will be invited to participate in this study, and will be followed up at 1, 6, 12, 24 and 36 months post-PCI to assess clinical outcomes.

The planned sample size is 175 subjects. We will recruit subjects with SVGD scheduled to receive PCI, aged 18–80 years, with a history of previous coronary artery bypass graft (CABG) surgery more than 1 year ago, and willing to participate in the study and sign informed consent.

The composite primary study endpoint is the incidence of MACEs after PCI for SVGD, including death from cardiac causes, non-fatal myocardial infarction, unplanned target lesion revascularization (TLR) and target vessel revascularization (TVR). The primary outcome analysis will be presented as Kaplan-Meier estimates and the primary outcome analysis will be carried out using a Cox proportional hazards regression model.

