### Sample size

We expect CAS of plaque and media 2.9 ± 1.7 mm^2^ among patients with MACEs and 1.9 ± 1.5 mm^2^ among patients without MACEs. It is estimated that the incidence of MACEs is 20% in 3 years after PCI for SVGD. Assuming a 20% drop-out rate, a total of 175 participants are required to provide 80% power, with a two-sided type I error of 0.05.

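### The primary composite (MACE) has one component list in the abstract and another in Study endpoints, and the 20% planning rate is tied to neither.

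*Protocol article*

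**What the plan says.** The protocol article names a single composite primary endpoint, the incidence of MACEs after PCI for vein graft disease, and lists its components twice.

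- **Abstract, Methods/design:** "including death from cardiac causes, non-fatal myocardial infarction, unplanned target lesion revascularization (TLR) and target vessel revascularization (TVR").
- **Methods and design, Study endpoints:** "including death from cardiac causes, non-fatal myocardial infarction, angina pectoris, target vessel revascularization (TVR) and hospitalization for heart failure".

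Study endpoints also defines one shared component: "TVR is defined as a new revascularization procedure in the target vessel".

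The Sample size section uses the term without a component list: "It is estimated that the incidence of MACEs is 20% in 3 years after PCI for SVGD". It plans on a difference in plaque-and-media area: "We expect CAS of plaque and media 2.9 ± 1.7 mm^2^ among patients with MACEs" against "1.9 ± 1.5 mm^2^ among patients without MACEs". It concludes that "a total of 175 participants are required to provide 80% power" with 20% drop-out and a two-sided 5% level. The Statistical analysis section applies Kaplan-Meier estimates and Cox models to three-year MACEs and adds ROC cut-offs, again without saying which list is meant.

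**The concern.** A study with two stated primary composites has no single pre-specified primary result. The choice decides who counts as a case, when the first event occurs, how many events enter the Cox model, how patients are grouped for the plaque comparison, and what the proposed prediction tool would predict.

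The extra components are not minor. Angina is a symptom-based event, and Baseline assessment and follow-up allows MACEs to be ascertained at a clinic visit or by telephone. That mode applies to every component, but it matters more for a symptom than for a death or a procedure.

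Timing adds weight. Trial status reports a first enrolment in July 2017 and 67 patients by August 2018, with follow-up visits at 1, 6 and 12 months. Some outcome data could therefore already exist while the article carries two definitions.

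**Working it through.** **1. The two lists side by side**

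| Component | Abstract | Study endpoints |
|---|---|---|
| Cardiac death | yes | yes |
| Non-fatal MI | yes | yes |
| Target lesion revascularization | yes, unplanned | not named, but inside TVR as defined there |
| Target vessel revascularization | yes; unclear whether unplanned applies | yes, any new procedure |
| Angina pectoris | no | yes |
| Hospitalization for heart failure | no | yes |

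A target lesion lies in the target vessel, so the absence of TLR from Study endpoints is mostly wording. On that section's TVR definition, the Study endpoints composite contains every event in the abstract's composite and adds angina and heart-failure hospitalization. Its rate is therefore at least as high. The two rates are equal only if no patient has an added event without also having a shared one.

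**2. Reproducing the 175**

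Inputs from Sample size: difference 2.9 - 1.9 = 1.0 mm²; SDs 1.7 and 1.5; MACE rate 20%, a 1:4 split; two-sided alpha 0.05; power 80%; drop-out 20%.

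- Patients with MACE = (1.960 + 0.842)² × (1.7² + 1.5²/4) / 1.0² = 7.849 × 3.4525 = 27.1, rounded up to 28.
- Evaluable patients = 28 / 0.20 = 140, that is 28 + 112.
- Enrolled = 140 / 0.80 = 175.

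The stated figure is matched exactly, and it depends on the 20%.

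**3. What follows if the 20% belongs to one list and the other list is used**

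The article gives no component rates, so the rates below are assumptions shown as ranges. The evaluable number stays at 140, and the planning means and SDs are applied to whichever composite is used, which is a further assumption. Power is for a two-sided Welch t-test, with noncentrality 1.0 / √(1.7²/n₁ + 1.5²/n₀). For 28 against 112 this is 1.0 / √(0.1032 + 0.0201) = 2.85.

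| Case | MACE / no MACE | Power |
|---|---|---|
| Planning case, 20% | 28 / 112 | 0.793 |
| 20% is the Study endpoints rate; abstract rate 15% | 21 / 119 | 0.682 |
| Same; abstract rate 10% | 14 / 126 | 0.508 |
| Same; abstract rate 8% (140 × 0.08 = 11.2) | 11 / 129 | 0.409 |
| 20% is the abstract rate; added components +10 points (30%) | 42 / 98 | 0.90 |
| Same; +25 points (45%) | 63 / 77 | 0.95 |

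The planning case gives 0.793 here and 0.81 under the normal approximation used in step 2. That gap comes from the method and is not a fault in the plan.

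In the last two rows the added patients number 42 - 28 = 14 and 63 - 28 = 35, which is 14/42 = 33% and 35/63 = 56% of all patients with MACE.

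**The case against.** The strongest reply is that the conflict need not damage the power claim. The composites are nested, so a reader who infers that 20% cannot describe both goes further than the documents allow: the rates coincide if the added components bring in no new patients. That is unlikely over three years, but no component rates are given to exclude it. A reader might also infer that the 80% power can hold for at most one composite. That fails too. If 20% is the abstract's rate and the planning difference carries over, the wider composite has power of about 90-95%.

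Three further points stand. Grammatically, unplanned in the abstract may govern TLR alone or TVR as well. The article mentions no staged procedures, so a planned repeat procedure could be read as an event under Study endpoints, but it is not shown that it would be. Nothing in the article ranks the abstract's list above the other, so a reviewer has no basis for choosing between them. Finally, selection of the composite after events are seen is a risk, not something shown; the registration and the full protocol may fix one list, and neither was available here.

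None of this removes the contradiction. Condensation into an article does not explain it, because both lists are printed in full and neither is a shortened form of the other.

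**Conclusion.** The point holds as an internal contradiction in the primary endpoint, and it must be resolved. The substantive differences are angina, heart-failure hospitalization and the unplanned condition. As written, the 20% rate, the MACE/no-MACE grouping, the Cox analysis and the ROC cut-offs are not attached to one endpoint.

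The sample size is not miscalculated. The power actually available depends on which list applies: roughly 41-68% on the unfavourable reading and 90-95% on the favourable one. Those ranges rest on assumed event rates, on the planning means and SDs holding for either composite although redefining MACE moves patients between the groups, and on a t-test where the primary analysis is a Cox model. They show how much hangs on the definition and do not predict the study's power.

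**What to change.** - Print one identical component list in the abstract and in Study endpoints: the composite in force when the first patient was enrolled, documented before any review of events.
- Say whether revascularization must be unplanned, and use the same TVR wording throughout. If the condition applies, confirm that planned or unplanned status is recorded, since the article does not say so.
- Report the components that appear only in the other list as secondary endpoints.
- In Sample size, state which composite the 20% describes. If it is not the primary one, restate the expected events and power.

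The cost is a clarification or short amendment and one recalculated line. The stated power may become less favourable.

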### Sample size

We expect CAS of plaque and media 2.9 ± 1.7 mm^2^ among patients with MACEs and 1.9 ± 1.5 mm^2^ among patients without MACEs. It is estimated that the incidence of MACEs is 20% in 3 years after PCI for SVGD. Assuming a 20% drop-out rate, a total of 175 participants are required to provide 80% power, with a two-sided type I error of 0.05.

### Statistical analysis

Analyses will be made using SAS statistical software (version 9.3) by researchers at the Peking University Clinical Research Institute. Continuous variables will be expressed as mean ± standard deviation or median ± interquartile range (IQR), and t-test or Wilcoxon rank sum test will be used to compare the difference between groups. For categorical variables, the chi-square test/ Fisher’s exact test will be performed. Time-to-event data (MACEs in 3 year after PCI) will be presented as Kaplan-Meier estimates and the primary outcome analysis will be carried out using univariate and multivariate Cox proportional hazards regression models. The ideal cut-off of quantitative indexes of VH-IVUS and the diagnostic accuracy will be determined by the receiver-operating characteristic curve (ROC). A *p*-value < 0.05 will be considered statistically significant in all analyses.

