### Participants

The patients to be included in the study should meet all of the following criteria: (1) aged 18–80 years; (2) a history of previous CABG surgery more than 1 year ago; (3) diagnosed as SVGD which is defined as at least one SVG ≥50% diameter stenosis; (4) plans for receiving PCI using drug-eluting stents; (5) willing to participate in the study and sign informed consent.

Patients will be excluded from the study if any of the following criteria is met: (1) acute myocardial infarction within the previous 7 days; (2) having any contraindication to aspirin, clopidogrel, heparin or stainless steel; (3) impaired renal or hepatic function; (4) history of cerebral stroke or ischemic cerebrovascular disease within 3 months; (5) history of gastrointestinal bleeding or hemoptysis in the previous 4 weeks; (6) pregnant or breastfeeding; (7) vasculitis or other non-atherosclerotic CAD; (8) other major illnesses that would expose the participant to unexpected risk: hematologic disorder, malignancy, etc.

Participants can withdraw from the study at any time without any adverse outcome on subsequent treatment; the reasons for withdrawal will be recorded. The investigator can also exclude a participant from the study for reasons including serious adverse events or poor compliance with research protocol.

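### Kaplan-Meier for a composite that counts only cardiac death would slightly overstate 3-year MACE incidence if non-cardiac deaths occur first; cumulative incidence is the better display

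*Protocol article*

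**What the plan says.** The protocol article defines the primary composite twice. Under Study endpoints it is MACE "including death from cardiac causes, non-fatal myocardial infarction, angina pectoris, target vessel revascularization (TVR) and hospitalization for heart failure". In the Abstract (Methods/design) it is MACE "including death from cardiac causes, non-fatal myocardial infarction, unplanned target lesion revascularization (TLR) and target vessel revascularization (TVR"). The two lists differ, which is a separate matter to reconcile. On the present point they agree: the only deaths that count are cardiac.

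Under Statistical analysis, "Time-to-event data (MACEs in 3 year after PCI) will be presented as Kaplan-Meier estimates". The Abstract also names Kaplan-Meier as the way the primary outcome will be presented. For inference, the Statistical analysis section turns to regression: "the primary outcome analysis will be carried out using univariate and multivariate Cox proportional hazards regression models". Under Sample size, "It is estimated that the incidence of MACEs is 20% in 3 years after PCI for SVGD".

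The article names no competing-risk method, gives no non-cardiac death rate, and does not write out how a non-cardiac death will be treated.

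**The concern.** The endpoint is worded as an incidence: the share of patients who have a MACE within 3 years. A patient who dies of a non-cardiac cause before any MACE can never contribute one. Kaplan-Meier has no separate state for that patient. It censors the follow-up and in effect assumes the same later MACE risk as in those still alive. The quantity estimated is then the risk in a hypothetical population in which nobody dies of other causes, and that risk is at least as large as the actual incidence.

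At stake is the accuracy of the reported 3-year MACE percentage and of the curves by plaque group. The estimated association between plaque features and MACE is not at stake. Eligibility covers patients "aged 18–80 years" with previous bypass surgery, followed for 36 months, so some non-cardiac deaths are plausible.

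**Working it through.** **1. The plan's own figure.** The inputs under Sample size are "We expect CAS of plaque and media 2.9 ± 1.7 mm^2^ among patients with MACEs" and "1.9 ± 1.5 mm^2^ among patients without MACEs", 20% MACE, 20% drop-out, 80% power and two-sided 0.05. For two means with unequal variances and a 1:4 split:

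n(MACE) = (1.960 + 0.842)² × (1.7² + 1.5²/4) / (2.9 − 1.9)² = 27.1, rounded up to 28.

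28 + 4 × 28 = 140, and 140 / (1 − 0.20) = 175.

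The stated 175 is reproduced. The calculation compares means and uses no Kaplan-Meier estimate, so the present point does not alter it.

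**2. Kaplan-Meier against cumulative incidence.** Inputs:

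- F = 0.20, the article's 3-year MACE figure, taken as the value of 1-KM.
- D = net 3-year risk of non-cardiac death. The article gives none, so D is an assumption, varied from 1% to 15%.
- Constant cause-specific hazards (a simplifying assumption): h1 = −ln(1 − F)/3 for MACE and h2 = −ln(1 − D)/3 for non-cardiac death.

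Formulas:

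- 1-KM = 1 − exp(−3·h1) = F
- Cumulative incidence = h1/(h1 + h2) × [1 − exp(−3(h1 + h2))]

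Worked case, D = 10%: 3·h1 = 0.2231 and 3·h2 = 0.1054. The ratio is 0.2231/0.3285 = 0.679. The bracket is 1 − 0.80 × 0.90 = 0.28. The product is 0.190, so Kaplan-Meier gives 20.0% where the actual incidence is 19.0%.

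| Assumed 3-year non-cardiac mortality | 1-KM | Cumulative incidence | Excess (points) | Excess (relative) |
|---|---|---|---|---|
| 1% | 20.0% | 19.9% | 0.1 | 0.5% |
| 3% | 20.0% | 19.7% | 0.3 | 1.5% |
| 5% | 20.0% | 19.5% | 0.5 | 2.5% |
| 10% | 20.0% | 19.0% | 1.0 | 5.2% |
| 15% | 20.0% | 18.5% | 1.5 | 8.0% |

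**3. Sensitivity to the event rate.** The list under Study endpoints includes angina and could yield more than 20%. As a pure assumption, with 1-KM at 40% the excess is 0.9, 1.9 and 2.8 points at 5%, 10% and 15% non-cardiac mortality. The article offers no figure of 40%.

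**4. Comparison with sampling error.** With 140 evaluable patients and a 20% estimate, the 95% half-width is 1.96 × √(0.20 × 0.80 / 140) = 0.066, or about 6.6 points.

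**The case against.** The strongest reply is that the article never says non-cardiac deaths will be censored. It is a condensed report, the analysis plan is not shown, and censoring rules commonly belong there. That is right as to the written rule. But the article does name the estimator, and an ordinary Kaplan-Meier for this composite leaves no other treatment of such deaths. An analysis plan could avoid the problem only by using a different estimator or a different endpoint. The point therefore concerns a stated choice.

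Size is the second reply, and it largely stands. The excess is about a point or less up to 10% non-cardiac mortality, well inside sampling error. The exclusions under Participants (malignancy, blood disorders, impaired renal or hepatic function, recent stroke) plausibly keep that mortality low, so nothing in the article supports the upper end of the assumed range. What remains is that the error has one direction, does not shrink as the sample grows, and lies outside what the confidence interval expresses.

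A reader might also infer more than the article supports:

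- **That the 3-year risk will certainly be overstated.** The excess arises only if a non-cardiac death before MACE is followed by another patient's first MACE. With no such deaths the two estimators agree.
- **That the planned prediction tool will be biased upward.** The Abstract and Conclusion mention a tool as a later prospect. Statistical analysis plans Cox models and ROC cut-offs. Nothing says the tool would report absolute risks or take them from Kaplan-Meier.
- **That older or sicker patients will be the most misjudged.** This would follow if their non-cardiac mortality is higher, but the article gives no figure and plans no curves for such subgroups.
- **That the primary association is compromised.** Censoring non-cardiac deaths in the Cox model gives a valid cause-specific hazard ratio.

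**Conclusion.** The point holds as a minor one. Kaplan-Meier does not match an incidence endpoint that excludes non-cardiac death, and any bias is upward. At the article's 20% MACE figure it amounts to roughly 0.1 to 1.0 percentage points for assumed 3-year non-cardiac mortality of 1% to 10%, and 1.5 points at 15%. These sizes rest on the assumed mortality, on constant hazards, and on non-cardiac deaths being censored as an ordinary Kaplan-Meier requires. The consequence is limited to the reported 3-year incidence and its curves. The change is worth making because it is nearly free, not because the study's conclusions depend on it.

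**What to change.** Present 3-year MACE as Aalen-Johansen cumulative incidence with non-cardiac death as a competing event, overall and for any plaque group for which curves are shown. Keep the Cox models, label their hazard ratios cause-specific, and state that non-cardiac deaths are censored there. If absolute risks are later derived for a prediction tool, compute them from the cause-specific hazards of both MACE and non-cardiac death.

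No new data are needed, because either version of the composite already requires deaths to be classified as cardiac or not. The cost is a few words in the analysis plan, one additional procedure, and a reported incidence that may come out slightly lower. The sample size stays at 175.

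### The VH-IVUS cut-off and its diagnostic accuracy come from the same ROC curve in one cohort, so sensitivity and Youden J at that cut-off will be overstated

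*Protocol article*

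**What the plan says.** The Statistical analysis section of the protocol article gives one sentence to cut-offs and accuracy: "The ideal cut-off of quantitative indexes of VH-IVUS and the diagnostic accuracy will be determined by the receiver-operating characteristic curve (ROC". The article describes one cohort at one hospital and mentions no validation set, sample split or resampling.

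The main analysis is a separate step. For display, the section says "Time-to-event data (MACEs in 3 year after PCI) will be presented as Kaplan-Meier estimates". For inference, it states that "the primary outcome analysis will be carried out using univariate and multivariate Cox proportional hazards regression models". Neither statement refers to the ROC cut-off. The section sets a 0.05 significance threshold for all analyses.

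The Sample size section supplies the planning values: "We expect CAS of plaque and media 2.9 ± 1.7 mm^2^ among patients with MACEs", compared with a planned "1.9 ± 1.5 mm^2^ among patients without MACEs". It adds "It is estimated that the incidence of MACEs is 20% in 3 years after PCI for SVGD" and, on losses, "Assuming a 20% drop-out rate". It then concludes that "a total of 175 participants are required to provide 80% power, with a two-sided type I error of 0.05". Trial status reports 67 patients enrolled between July 2017 and August 2018, with follow-up until December 2021. The Discussion of the abstract and the Conclusion say that a confirmed result would lead to a prediction tool for stratifying risk and guiding intervention.

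**The concern.** A cut-off chosen because it separates the events best in a given set of patients has partly been fitted to chance in those patients. Sensitivity and specificity read off the same curve are then too favourable, and the fewer the events, the larger the excess. About 28 events is few. The cut-off itself is also poorly determined, so a single ideal value without an interval would suggest precision that the data lack.

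These are the figures most likely to be carried into a prediction tool. If they are optimistic, the tool will do worse in new patients than the publication says.

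A second, smaller matter is that MACE over 3 years is a time-to-event outcome, while the ROC sentence gives neither a time point nor a way of handling patients whose 3-year status is unknown.

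**Working it through.** **1. The plan's own sample size.** Inputs, all from the Sample size section: means 2.9 and 1.9 mm² (difference 1.0), SDs 1.7 and 1.5, MACE incidence 20% (ratio 1:4), drop-out 20%, power 80%, two-sided 0.05. Normal approximation with unequal variances:

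- n(MACE) = (1.960 + 0.842)² × (1.7² + 1.5²/4) / 1.0² = 7.85 × 3.4525 = 27.1, rounded up to 28.
- Total = 28 × 5 = 140, and 140 / (1 − 0.20) = 175.

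The stated 175 is reproduced. The working split is 28 patients with MACE and 112 without.

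**2. Optimism at the cut-off.** Simulated studies drew 28 and 112 normal values with the plan's means and SDs and took the cut-off c that maximises J = sensitivity + specificity − 1. The apparent values were compared with the true values at the same c:

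- true sensitivity = 1 − Φ((c − 2.9)/1.7)
- true specificity = Φ((c − 1.9)/1.5)

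| Averages (10,000 studies) | Apparent | True at chosen cut-off |
|---|---|---|
| Sensitivity | 0.64 | 0.56 |
| Specificity | 0.69 | 0.67 |
| Youden J | 0.33 | 0.23 |
| AUC | 0.670 | 0.670 |

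The excess in J is 0.33 − 0.23 = 0.10, about 30% of the apparent value (0.10/0.33). The best J attainable with these distributions is 0.25, at 2.68 mm², so the apparent 0.33 exceeds even what a perfectly placed cut-off could achieve. The true AUC is Φ(1.0/√(1.7² + 1.5²)) = Φ(0.441) = 0.670, which the sample AUC matches on average. The optimism therefore belongs to the chosen cut-off, not to the curve as a whole.

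**3. Stability of the cut-off.** The central 95% of chosen cut-offs runs from about 1.3 to 4.1 mm². This is wider than the gap between the two planned group means, 1.9 and 2.9.

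**4. Sensitivity to the normal assumption.** A normal marker with mean 1.9 and SD 1.5 puts Φ(−1.9/1.5), about 10%, of the MACE-free patients at impossible negative areas. With non-negative gamma markers of the same means and SDs, J is 0.37 apparent against 0.27 true, and the cut-off ranges from about 1.0 to 3.2 mm². The optimism is again about 0.10.

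**5. Censoring.** Assumptions: event times and non-informative drop-out times uniform over 36 months, 175 enrolled, 175 × 0.20 = 35 MACEs if all were followed.

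- With 20% drop-out, about 31.5 of the 35 events are seen. Scoring the censored patients as event-free gives AUC 0.664 against 0.669 with full follow-up.
- Enrolment pace: 67 over about 13.5 months is 4.96 per month. If constant (an assumption), 175 is reached after 175/4.96 = 35.3 months. December 2021 is about month 53.5, so the last patient has 53.5 − 35.3 = 18.2 months of follow-up. Only those enrolled by December 2018, about 17.5 × 4.96 = 87, can reach 36 months.
- With drop-out and this end date together, about 27.9 of 35 events are seen, about 52% of patients are event-free with less than 36 months of follow-up, and AUC is 0.663 against 0.671.

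**6. If the cut-off were tested.** With no marker effect at all, an unadjusted 0.05 chi-square test at the Youden cut-off rejects in about 23% of studies when the direction is fixed in advance and about 39% when the data choose it.

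**The case against.** The strongest reply is that this is a condensed article. Bootstrap correction, a time-dependent ROC and an interval for the cut-off are details that a full analysis plan often holds, and the text does not rule them out. It does not say that the ROC is of the ordinary kind, and it does not name the outcome. The ROC might serve slow/no reflow within 24 hours or successful reperfusion, where 3-year censoring does not arise. This stands in part: that censoring is ignored cannot be asserted, only that the sentence leaves it open. It does not dispose of the main point, which rests on something the plan states: one curve sets both the cut-off and its accuracy.

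Two stronger readings are tempting, and the documents support neither.

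- A reader might infer that significance tests at the cut-off will have inflated type I error, since Kaplan-Meier curves for a continuous index need groups. No log-rank or other test at the cut-off is stated, and the Cox model is not tied to it. The Kaplan-Meier estimates could be overall, or by the plaque classes that the VH-IVUS section defines in advance. The 23% to 39% is therefore conditional.
- A reader might infer that ignoring censoring makes accuracy look better. Under non-informative censoring the AUC moves slightly down, by under 0.01.

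It is also fair to say that the Youden criterion is assumed, that specificity is barely affected (0.69 against 0.67), and that the article makes the prediction tool conditional on the hypothesis being confirmed.

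**Conclusion.** The point holds in a limited form. Choosing the cut-off and reading its accuracy from the same roughly 28 events overstates sensitivity by about 0.08 and Youden J by about 0.10, and the cut-off is too unstable to be reported as a single value. This rests on the plan's means, SDs and incidence and on a Youden rule; the optimism in J is the same for normal and gamma markers. The AUC of one index with a pre-set direction is not biased.

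Censoring is a separate and secondary matter. It does not inflate accuracy, but a yes/no 3-year MACE status will be missing for some patients, possibly about half under the assumed constant enrolment pace, so 3-year sensitivity and specificity are not well defined without a method that handles it. The primary Cox analysis is not affected by either problem as written.

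**What to change.** Amend the ROC sentence, or confirm that the full analysis plan already says the following:

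- Repeat the cut-off selection within bootstrap samples. Report optimism-corrected sensitivity and specificity and an interval for the cut-off.
- For MACE, use a time-dependent ROC at 36 months with inverse-probability-of-censoring weights.
- Keep each VH-IVUS index continuous in the Cox model.
- Label the cut-off exploratory, and attach no unadjusted p-value to groups formed at it.

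No new data are needed. The cost is a few sentences, modest programming and reported accuracy that looks less favourable.
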